##### Data sources differ according to the population

Table 1 also gives an overview of the available data sources for each aspect of the Quadruple Aim and for the different samples. The primary data source for the outcome evaluation will be the Inter Mutualistic Agency (IMA-AIM) data warehouse, which contains data on all reimbursed health interventions, e.g., general practitioner and specialist visits, technical and diagnostic interventions, hospital and emergency admissions, and medication. These data are available for the whole target population (population A, see Table 1). For the included population (population B), the long-term aim is to link individual IMA data with other data sources, such as hospital data, data extracted from General Practitioner Electronic Medical Files and survey data from the Belgian Resident Assessment Instrument (BELRAI) screener [49,50]. It should be noted that BELRAI results will enable a risk and frailty classification [51]. To complement the administrative data, both patients and care providers involved in the ICPs will be surveyed. An invitation letter will be sent or given to all included patients. This letter will include a link to an encrypted, secured website with the PROM and PREM questionnaires, namely, the 5Q-5D-5L questionnaire [52] and the Patient Assessment of Chronic Illness Care (PACIC) questionnaire [53]. Both questionnaires have been translated and validated in French and Dutch.

A subsample of professional care providers (Population C) involved in an ICP will be asked to participate in a web survey to evaluate (a) job satisfaction, which will be assessed by a portion of the RN4Cast-research questionnaire [54]; (b) burnout, which will be assessed by the UBOS questionnaire [55]; and (c) relational coordination [56]. Due to the small sample size and/or the expected high turnover of patients and professionals, it will not be possible to perform a longitudinal study using this data.

#### Indicators

##### Quadruple Aim indicators

A set of Quadruple Aim indicators was developed. In total, nearly 300 parameters were selected for analysis in consultation with all the stakeholders and based on the consensus in the literature on the Quadruple Aim [57,58], action plans of the ICPs, government objectives, existing methodology and criteria on quality indicator selection [59,60] and feasibility. Table 2 gives a non-exhaustive selection of the most relevant indicators.

**Table 2 T2:** Overview of the most relevant Quadruple Aim indicators and samples of interest.

Domain and indicator	Numerator	Denominator	Data Source	Sample

**Population Health**				
Mortality	Number of deaths	Total population & population stratified by age and subgroups	IMA	A/B
Occupational disability	Number of people who have reported a lapse in professional occupation due to health issues during the last 12 months	Active population stratified by the criteria mentioned later	IMA	A/B
Activities of daily living (ADL) & instrumental activities of daily living (IADL)	Number of people with ADL > 3/IADL after 1 year	Total number of patients stratified by subgroups	BELRAI	B
Mobility, self-care, usual activities, pain & discomfort, anxiety & depression	Number of people with no or slight problems	Total number of patients in Sample C	EQ-5D-5L**	B
Quality of life on a visual analogue scale	Number of people with a self-reported quality of life > 80	Total number of patients in Sample C	EQ-5D-5L	B
**Patient Experiences**				
PACIC domains (4): Patient activation; delivery system design; goal setting; problem solving	The average percentage of patients who respond “most of the time” for each domain	Total number of people in the sample	PACIC**	B

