## Results: the research protocol

### Research questions

Based on the requirements of the government plan, Faith.be defined common research questions for each ICP, all related to the Quadruple Aim:

What changes have occurred over time in the health of the population of the projects?What changes have occurred over time in the cost of care, more specifically regarding the indicators of low- and high-value care?What changes have occurred over time in the Patient Reported Experience Measures (PREMs)?What changes have occurred over time in the indicators of professional functioning and wellbeing?

Furthermore, an in-depth explanatory analysis will answer questions regarding the implementation of these complex interventions in their particular loco-regional contexts and the association between the implementation processes and the achievement, or lack thereof, of the predefined outcome objectives. These questions are as follows:

5. What factors enabled an ICP to achieve its Quadruple Aim objectives and the 14 components of integrated care or hindered it from doing so in its local context? Which objectives were achieved? Which objectives were not achieved? For whom? How and why? To which unintended consequences has the ICP led?6. Which adaptations were needed to reach those objectives? Why and when were these adaptions made and with what means/resources?7. How do healthcare professionals in ICPs experience the ICP? More specifically, based on Normalization Process Theory,Do they understand and agree with the programme (*Coherence*)?Are they led and recognized when becoming involved with the programme (*cognitive participation*)?Do they see positive changes in their work activities (*collective action*)?Do they have the means to learn from what they are doing (*reflexive monitoring*)?

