**Professional Well Being**				
Indicator	Numerator	Denominator		
Relational coordination	Number of providers who indicate that they often or always collaborate	Total number of providers	RC survey	C
Job satisfaction	Average number of providers who respond “Satisfied” or “Very satisfied” for select indicators of job satisfaction	Total number of providers	4N4Cast	C
Burnout	Average number of providers who respond “Often”, “Very often” or “Always” for select indicators of UBOS	Total number of providers	UBOS	C

* Population A includes population B. ** Self-Reported. **** Serving as an indicator for equity [62]. **** SES = Socio Economic Status.

The evaluation of population health will be based on diagnoses and specific care needs. Costs will be calculated using specific claims codes (called medical nomenclature codes) and will be interpreted and aggregated into specific cost components with the intention of monitoring potential transfers of a patient’s healthcare cost to different healthcare professionals or healthcare providers (e.g., a transfer from hospitalization cost to in-home care cost). Efficiency and equity will be evaluated indirectly according to the value-based healthcare concept (VBHC). The use of “high-value care” (in contrast to “do-not-do care” or “low-value care”) will serve as a proxy measure for efficiency and equity. Low-value services are related to misuse, overuse or underuse of health services. Do-not-do care refers to the NICE ‘do not do’ recommendations [61]. High-value care that is not used by people in need with given characteristics (a specific disease or a specific socioeconomic status) will be used as a proxy for equity. In addition, a care trajectory analysis for subgroups of patients will be performed. This means that based on the literature and expert opinion, ‘high-value’ sequences of care will be defined according to their expected impact on (better) health outcomes and/or (lower) costs. An example of high-value care is a general practitioner visit within 7 days after hospitalization for people with frailty. Once defined, these sequences can be analysed and compared over time and between ICPs.

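### Table 2 counts only the PACIC answer 'most of the time'; if the scale has a better answer, the indicator could fall while patient experience improves

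*Protocol article*

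**What the plan says.** In the protocol article, Table 2, Patient Experiences, the single row covers four PACIC domains and defines the numerator as "The average percentage of patients who respond “most of the time” for each domain". The denominator is everyone in the sample.

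The other ordinal survey rows of Table 2 are worded differently:

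- EQ-5D-5L dimensions (Population Health): "Number of people with no or slight problems"
- Relational coordination (Professional Well Being): "Number of providers who indicate that they often or always collaborate"
- Job satisfaction (Professional Well Being): "Average number of providers who respond “Satisfied” or “Very satisfied” for select indicators of job satisfaction"
- Burnout (Professional Well Being): "Average number of providers who respond “Often”, “Very often” or “Always” for select indicators of UBOS"

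The section on data sources by population names the PACIC questionnaire and cites a reference for it, but does not list its answer options. The Research questions section gives the question that this row serves, the third: change over time in patient-reported experience measures.

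**The concern.** An indicator used to follow change should move in one direction as the thing it measures improves. The share giving one particular answer has that property only if the answer is the end of the scale. In ordinary language 'most of the time' falls short of 'always', and two provider rows of the same table use 'always' as their end point. If PACIC has such an answer, a patient who moves up to it drops out of the numerator and is grouped with those who answered below 'most of the time'.

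At stake is how the yearly PACIC figures are read for research question 3. The design offers little to expose a wrong direction:

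- The section on difference-in-differences analyses limits the comparison with non-ICP residents to the insurance data.
- The section on populations of interest says that the insurance database is the only source for the baseline period.
- The section on data sources rules out a longitudinal study of the survey data, so individual upward moves cannot be followed.

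**Working it through.** The article gives no PACIC rate, so there is no figure to reproduce. The check has two parts.

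**1. Wording of the ordinal survey rows in Table 2**

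| Row | Answers counted | Reaches the end of the scale? |
|---|---|---|
| EQ-5D-5L dimensions | no, slight | yes (best end) |
| Relational coordination | often, always | yes |
| Job satisfaction | satisfied, very satisfied | yes |
| Burnout | often, very often, always | yes (worst end) |
| PACIC domains | most of the time | not stated; one answer only |

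PACIC is the only one of these rows that counts a single answer.

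**2. Behaviour of a single-answer share**

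Assumptions, none of them from the article: five ordered levels, with 'most of the time' at level 4 and one better answer at level 5. The assumed starting distribution over levels 1 to 5 is 10%, 15%, 25%, 30%, 20%. Let *a* be the fraction of level 3 that moves to level 4, and *b* the fraction of level 4 that moves to level 5. Nobody gets worse.

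- Indicator as written = 30 + 25*a* − 30*b* (percent)
- Cumulative share (level 4 or 5) = 50 + 25*a* (percent)
- Mean level = 3.35 + 0.25*a* + 0.30*b*

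| *a* | *b* | As written | Cumulative | Mean level |
|---|---|---|---|---|
| 0 | 0 | 30% | 50% | 3.35 |
| 0.2 | 0 | 30 + 5 − 0 = 35% | 50 + 5 = 55% | 3.40 |
| 0.2 | 0.3 | 30 + 5 − 9 = 26% | 50 + 5 = 55% | 3.49 |
| 0 | 0.1 | 30 + 0 − 3 = 27% | 50% | 3.38 |
| 0 | 0.5 | 30 + 0 − 15 = 15% | 50% | 3.50 |

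The indicator as written falls when 30*b* > 25*a*, that is, when the outflow to the better answer exceeds the inflow from below. With *a* = 0.2 the break-even is *b* = 5/30 = 0.167. The second and third rows have the same cumulative gain, and the third has the larger gain in mean level, yet the indicator moves in opposite directions. The cumulative share never falls when patients only improve.

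The row speaks of an average percentage for each domain. Averaging single-answer shares over the items of a domain does not remove the problem, because each share that is averaged has it.

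If 'most of the time' were the top level, *b* could not exceed 0. The share as written and the cumulative share would then be the same number.

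**The case against.** **The scale is not in the article.** This stands. That a better answer exists is inferred from the wording and from the other rows, so the consequence has to be stated conditionally. A reader might infer that the indicator is certainly not monotone; the article does not show that.

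**A fall is not inevitable.** This also stands. With enough inflow from lower answers the indicator rises, as in the 35% case. The percentages are illustrative and say nothing about what PACIC will show in these projects.

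**Research question 3 may not rest on this row alone.** A reader might infer that the answer to that question would be reversed. The article does not support this: Table 2 is described as a non-exhaustive selection from nearly 300 parameters, so other PACIC summaries may exist. What stands is that this is the only patient-experience row among those presented as most relevant.

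**The cell may be shorthand in a condensed article.** This is possible, and the full indicator definitions are not shown. But the article does not leave the numerator to another document. It states one, and words it differently from all the other ordinal survey rows, which spell out their answers in the same space. As printed it is a definition, and someone programming the monitoring system could apply it literally.

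**The reach is limited.** Agreed. The row feeds descriptive yearly monitoring. No sample size, test or error rate depends on it, and the article expects further adaptation of the protocol, with the surveys already changed during design. That makes correction easy; it does not make the present wording safe.

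**Conclusion.** The point holds in conditional form. Table 2 fixes the PACIC numerator as one answer, while all other ordinal survey rows run to the end of their scale. If PACIC has an answer more favourable than 'most of the time', the indicator could fall while experience improves, namely when more patients move out to the better answer than move in from below. On the assumed scale and starting distribution, the same rise in the cumulative share goes with anything from a 4-point fall to a 5-point rise in the indicator, depending only on how many patients at 'most of the time' improve further (30% or none). The size in practice is unknown, because the article gives neither the answer options nor any PACIC distribution. It is a definition to correct before the yearly PACIC figures are used for research question 3.

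**What to change.** In Table 2, Patient Experiences, define the numerator as patients who answer 'most of the time' or any more favourable category, averaged within each domain as now, and state the PACIC answer options beside it. This brings the row into line with the other ordinal survey rows. The denominator can stay as it is for this purpose. Reporting the mean domain score as well is optional.

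The cost is one table line and the matching line in the indicator specification. No new data or change to the questionnaire is needed. If 'most of the time' is the top answer, the new definition gives the same figures as the present one.

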**Cost efficiency, care with high and low value and equity**				
ED visits and hospitalization through the emergency department (per 1000) during the last 12 months	Number of episodes during the last 12 months	Total population & population stratified by subgroups (Rate)	IMA	A/B
Number of early 30-d readmissions (per 1000) in the last 12 months due to Xi disease	Number of early 30-d readmissions in the last 12 months	Total population & population stratified by subgroups (Rate)	IMA	A/B
Number and indices of n° of specialized visits/GP visits***	Number of outpatient specialized visits in the last 12 months in a given person’s profile	Total population & population stratified by subgroups & by SES**** (Rate)	IMA	A/B
Number of dental visits per year****	Number of early 30-d readmissions in the last 12 months	Stratified by SES		
Proportion of patients using ≥5/10 drugs (per 1000), last 12 months, due to any cause	Number of patients using ≥5/10 drugs, last 12 months, due to any cause	Total population & population stratified by subgroups	IMA	A/B
Proportion of patients with ≥2 ER consultations during a 6 months period, last 12 months	Number of patients with ≥2 EM consultations during a 6 months period, last 12 months	Total population & population stratified by subgroups	IMA	A/B
**Professional Well Being**				
Indicator	Numerator	Denominator		
Relational coordination	Number of providers who indicate that they often or always collaborate	Total number of providers	RC survey	C
Job satisfaction	Average number of providers who respond “Satisfied” or “Very satisfied” for select indicators of job satisfaction	Total number of providers	4N4Cast	C
Burnout	Average number of providers who respond “Often”, “Very often” or “Always” for select indicators of UBOS	Total number of providers	UBOS	C

* Population A includes population B. ** Self-Reported. **** Serving as an indicator for equity [62]. **** SES = Socio Economic Status.

The evaluation of population health will be based on diagnoses and specific care needs. Costs will be calculated using specific claims codes (called medical nomenclature codes) and will be interpreted and aggregated into specific cost components with the intention of monitoring potential transfers of a patient’s healthcare cost to different healthcare professionals or healthcare providers (e.g., a transfer from hospitalization cost to in-home care cost). Efficiency and equity will be evaluated indirectly according to the value-based healthcare concept (VBHC). The use of “high-value care” (in contrast to “do-not-do care” or “low-value care”) will serve as a proxy measure for efficiency and equity. Low-value services are related to misuse, overuse or underuse of health services. Do-not-do care refers to the NICE ‘do not do’ recommendations [61]. High-value care that is not used by people in need with given characteristics (a specific disease or a specific socioeconomic status) will be used as a proxy for equity. In addition, a care trajectory analysis for subgroups of patients will be performed. This means that based on the literature and expert opinion, ‘high-value’ sequences of care will be defined according to their expected impact on (better) health outcomes and/or (lower) costs. An example of high-value care is a general practitioner visit within 7 days after hospitalization for people with frailty. Once defined, these sequences can be analysed and compared over time and between ICPs.

##### Process Indicators

Process indicators will allow us to evaluate the reach of the ICPs and determine which specific actions that individual patients are benefitting from within the ICPs, which are important elements of the implementation analysis. Some of these indicators will be calculated based on external data sources (see Table 3), and other indicators will be calculated based on the data collected by the ICP. Some of the process indicators listed in Table 3 will be collected among all ICPs. For the activities that are not common to all ICPs, project-specific indicators will be collected.

**Table 3 T3:** Key process indicators common to all ICPs.

Action	Indicator

Inclusion	% of included patients (with informed consent)
Medication review	Relative share of medication that was prescribed using the International Non-proprietary Name (INN)
Training sessions for professionals	Number of training sessions organized
	Number of professionals (per type) who participated
Training sessions for patients	Number of training sessions organized
	Number of patients who participated
Case management	Number of patients in a case management trajectory
Case management	Case load: Number of patients in case management/number FTE case managers
Care pathways	Number of pathways
	Number of patients in each pathway

##### Difference-in-differences analyses

The question of *whether* significant change in relevant Quadruple Aim indicators has occurred will be evaluated through a before/after comparison and a difference-in-differences (DID) analysis of the target population and the included population of the ICPs with a non-ICP comparison group. This will only be possible for data from the IMA warehouse (see Tables 1 and 2) since those data are available for the whole Belgian population. As such, all people living in Belgium outside an ICP region constitute the pool for comparison. Similar quasi-experimental designs have been used during the evaluation procedures of other natural experiments [63], defined as deliberate events, programmes or (complex) interventions. *“Exposure to the events or interventions has not been manipulated by the researcher”* in these designs [63]. Direct matching, propensity score matching, or group comparison with adjustment for confounders are possible comparison methods. The aim is to reduce the observed and unobserved confounding factors. Since this model deals with dynamic cohorts (new participants will be added to the target, the included and the comparison populations over time) for which it is not clear how to implement matching techniques [64,65,66,67,68], we opted for a group comparison by means of a generalized linear model for correlated longitudinal data and adjustment for confounders.

### Integrative mixed methods: context-mechanisms-outcomes analysis to explain the observed changes

To obtain insight into *how* Quadruple Aim outcomes will be reached, it will be necessary to combine qualitative and quantitative analyses. Mixed methods bring together qualitative and quantitative approaches into a single study and rely upon the complementary strengths of each approach to address the study questions [69]. Quadruple Aim outcomes must be considered ‘distal outcomes’ [70] and are not expected to change significantly in the first years after the start of the implementation [71]. In the meantime, the process indicators can be collected and analysed to explore the short-term changes. For this, we will use realist evaluation to identify context-mechanisms-outcomes configurations (CMOCs) explaining whether and to what extent the interventions of the programmes, or parts of these programs, were successful. Through the analysis of both the qualitative and quantitative data collected from the patients, care providers and coordinators of the ICPs, mid-range theories will be developed and tested. The aim of these theories will be to explain the contextual factors and mechanisms by which ICPs may evolve towards better care integration and improved Quadruple Aim outcomes [72]. Qualitative analyses will be based on the results of focus groups, significant event reports, interviews, learning community meetings, key documents such as the annual reports and other documentation of the ICPs. The insights, as they develop, will constantly be compared among all ICPs to allow for the identification and testing of the logic of the interventions in each context [73]. For example, explorative CMO multivariate analyses will be performed comparing the evolution of different ICPs, and these results will be discussed during reflective meetings within the learning communities. This will lead to the further refinement of our theory and the identification of context-mechanisms-outcomes configurations explaining the success– or failure of the programme interventions. These steps will be refined through their comparison with the results of other ICPs; repeated discussions within the multidisciplinary research team; and consultation with international reviewers, stakeholders of the ICPs and the government. The order of these steps will, however, vary, as realist evaluations intertwine between theoretical concepts emerging from qualitative analyses and literature with preliminary findings from empirical data. The analysis of the data will lead to insights that will be fed back to the ICPs and can help them in their work.

As such, the quantitative outcome analysis and the realist evaluation are combined in a sequential triangulation with a cyclical nature [74].

